## 15.2 Assessment of adverse events severity and relationship to treatment

For toxicity evaluation and grading of each AE, all the investigators will refer to the NCI Common Toxicity Criteria Version 3.0, available on-line (Appendix D).

For adverse events not covered by the common toxicity criteria, the following definitions will be used:

- Mild (G1): awareness of sign, symptom or event, but easily tolerated.
- Moderate (G2): discomfort enough to cause interference with usual activity and may warrant intervention.
- Severe (G3): incapacitating with inability to do usual activities or significantly affects clinical status, and warrants intervention.
- Life-threatening (G4): immediate risk of death.
- Causing death (G5).

The investigator, based on available information, will assess the relationship of any AE to the use of sorafenib and/or vinorelbine. A causal role of each drug will be defined according to the following guidelines:

- Likely: temporal association, other etiologies unidentified and unlikely.
- Possible: temporal association, but other etiologies are likely the cause; however, involvement of the drug cannot be excluded.
- Unlikely: no temporal association, or the cause of the event has been identified, or the drug cannot be implicated.

All AEs, including abnormal laboratory values, will be recorded on the adverse event module.

## 15.3 Monitoring adverse events

Patients reporting an AE will be monitored with appropriate clinical assessments and laboratory tests, as determined by the treating physician.

All adverse events must be followed to satisfactory resolution or stabilization, also after patient's withdrawal from the study.

Any measures taken and follow-up results will be recorded on the data collection form, as well as in the patient's source document. Follow-up laboratory results should be filed with the patient's source documentation.

## 15.4 Definition of Serious Adverse Event (SAE)

A serious adverse event (SAE) is any adverse event that results in any of the following

outcomes:

- death;
- life-threatening AE (that places the subject, in the view of the initial reporter, at immediate risk of death from the AE as it occurs, i.e., suicidal ideation/suicide attempt);
- persistent or significant disability/incapacity;
- required in-patient hospitalization, or prolonged hospitalization, with exceptions listed below;
- congenital anomaly or birth defect.

Additionally, important medical events that may not result in death, be life-threatening, or require hospitalization may be considered a SAE when, based upon appropriate medical judgment, they may jeopardize the subject and may require medical or surgical intervention to prevent one of the outcomes listed in this definition.

Examples of such medical events include allergic bronchospasm requiring intensive treatment in an emergency room or at home, blood dyscrasias, or convulsions that do not result in in-patient hospitalization, or the development of drug dependency or drug abuse.

“Serious” and “severe” as stated on the AE collection form are not synonymous. Severity refers to the intensity of a reaction (i.e., mild, moderate, severe, etc.). “Serious” refers to a regulatory definition for the outcome of an event (i.e., fatal, life-threatening, resulted in hospitalization, etc.).

If a subject has a preplanned hospitalization or procedure (e.g., elective surgery) during the study for an event, which occurred before the study start, the hospitalization is considered a therapeutic intervention and not an SAE. However, the event and/or the procedure must be reported in the CRF.

An AE requiring/prolonging in-patient hospitalization will not be considered a SAE for this study if the only reason for the hospitalization or prolongation is one of the following ones:

- administration of chemotherapy;
- transfusion of blood products;
- administration of study procedure;
- placement of a permanent intravenous catheter;
- hospice placement for terminal care

## 15.5 Report of Serious Adverse Events (SAEs)

Reports of all SAEs, including deaths must be communicated to the appropriate

Institutional Review Board or ethical review committee and/or reported in accordance with local law and regulations.

Any serious adverse event (SAE), whether or not deemed drug-related or expected, must be reported by the physician immediately or within 24 hours to:

**Questions to:**  
DSI [contact]

If the report is made via telephone, a written report must follow as soon as possible, which includes a full description of the event and any sequelae. SAEs that occur at any time after the inclusion of the subject in the study (defined as the time when the subject signs the informed consent) up to 30 days after the subject completed or discontinued the study must be reported.

The subject is considered to have completed the study either after the completion of the last visit or contact (eg, phone contact with the investigator), or after the last dose of study medication, whichever is later.

The date of discontinuation is when a subject and/or investigator determines that the subject can no longer comply with the requirements for any further study visits or evaluations (e.g. the subject is prematurely discontinued from the study).

## **15.6 Reporting of a subject's death**

The death of any subject during the study or within the 30 days post-treatment period following study completion (as defined above), regardless of the cause must be reported as a SAE within 24 hours to:

**Questions to:**

DSI [contact]

If the report is made via telephone, a full written report (SAE form and death page from the CRF) must follow as soon as possible. The death must be recorded in the patient chart and on the CRF. If an autopsy is performed, the report must be provided to McGill University, Department of Oncology and Bayer Canada.

After 30 days from study completion, a patient's death will be reported for regular follow-up purposes, but will not be reported as a SAE, unless considered by the investigator possibly related to a previous study-related AE.

**15.7 Report of pregnancies**

Although not considered a SAE (unless an event occurs with a serious outcome), if a subject should become pregnant during the course of the study, it must be reported within 24 hours to:

**Questions to:**

DSI [contact]

Bayer representatives will provide instructions on how to collect pregnancy information.

If a pregnancy occurs in a subject, study drugs should be discontinued. Follow-up information on the outcome of the pregnancy should also be forwarded to the sponsor.

**16. STATISTICAL CONSIDERATIONS**

## 16.1 Sample size justification for Phase II

A pooled analysis of data available in the literature was performed, selecting for phase II trials with vinorelbine administered as monotherapy as first-line treatment for metastatic breast cancer. From this analysis, an overall response rate of 43.2% is estimated as representative of vinorelbine single-dose activity in this type of patients (188 objective responses out of 435 evaluable patients).

The combination with sorafenib, increasing vinorelbine efficacy, is reasonably expected to improve the response rate compared to vinorelbine monotherapy. Even though the attainment of an objective response does not directly correlate with a real survival advantage for patients, the higher is the advantage in overall response rate for the combination therapy, the more suggestive this would be of a clinical promising synergism.

It is felt that if the two drugs combination would lead to an increase from ~43% to 63% of response rate (+ 20%), this would compel us to further investigate the activity in a randomized trial.

Sample size for the Phase II was determined using simulation, to obtain a power of 80% in order to detect such an increase in response rate with a significance level ( $\alpha$ ) of 0.10.

Based on this assumption, the minimum sample size would be 27 evaluable patients, as shown below:

QuickTime™ and a  
TIFF (LZW) decompressor  
are needed to see this picture.

A binomial test with a nominal 0.10 one-sided significance level will have the power as shown below for various response rates to test the Null hypothesis response rate of 43%, with a sample size of 27 patients.

| Null hypothesis response rate (p0) | Alternative hypothesis response rate (p1) | Power |
|------------------------------------|-------------------------------------------|-------|
| 43%                                | 53%                                       | 40%   |
| 43%                                | 58%                                       | 61%   |
| 43%                                | 63%                                       | 80%   |
| 43%                                | 68%                                       | 92%   |

Standard software package nQuery Advisor was used to calculate the sample size required for this trial.

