### 9.2 Phase II

In the second part of the trial, the cohort of patients treated at the RD will be expanded, up to a total of 27 patients treated with vinorelbine 30 mg per square meter (days 1, 8 q21) plus sorafenib at the RD.

Six patients in this expanded cohort will undergo sample collection for pharmacokinetic analysis of vinorelbine and sorafenib.

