#### **16.4 Analysis of primary endpoints**

Confirmed objective responses and stable diseases will be calculated, to determine objective response rate (ORR) and clinical benefit rate (CBR). The 95% confidence interval for ORR and CBR will be constructed using the exact methods.

ORR is defined as the proportion of subjects with confirmed CR or confirmed PR according to the RECIST criteria, relative to the total subjects who receive at least 1 dose of study medication(s).

CBR is defined as the proportion of subjects with clinical benefit response, relative to the total subjects who receive at least 1 dose of study medication(s).

Patients who do not have on-study radiographic tumor re-evaluation (or clinical re-evaluation, when physical examination is indicated to monitor disease state) will be counted as non-responders/non-benefiters in the assessment of ORR and CBR, unless replaced through enrollment of extra-evaluable patients.

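### The 43% null and the 27 patients are set per evaluable patient, but ORR is defined per patient dosed, and an open-ended replacement clause leaves the denominator unsettled

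*Protocol*

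**What the plan says.** Four parts of the Protocol bear on the denominator.

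- **Section 16.1, null.** The vinorelbine benchmark is a pooled 43.2%, from "188 objective responses out of 435 evaluable patients".
- **Section 16.1, size.** The design aims "to obtain a power of 80" per cent for a rise from about 43% to 63%, and concludes that "the minimum sample size would be 27 evaluable patients". The test is described as "A binomial test with a nominal 0.10 one-sided significance level", and its power table uses 27 patients. An increase of this size is what would lead to a randomized trial.
- **Sections 16.3 and 16.4, analysis.** Objective response is analysed in, and ORR is a proportion of, all subjects with at least one dose. Patients with no on-study re-evaluation "will be counted as non-responders/non-benefiters in the assessment of ORR and CBR". The same sentence excepts those replaced by enrolling extra evaluable patients.
- **Sections 6 and 9.2, enrolment.** The cohort at the recommended dose is expanded "up to a total of 27 patients treated with vinorelbine 30 mg per square meter" plus sorafenib.

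Section 16.4 itself specifies only exact 95% confidence intervals. The test against 43% is stated only in 16.1.

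**The concern.** The benchmark leaves out patients who could not be evaluated. By default the trial's ORR keeps them in and counts them as failures. A treated but unassessed patient therefore weighs against the combination, although such patients were not in the denominator that produced 43%.

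A cohort of 27 treated also leaves no margin for reaching 27 evaluable. The replacement clause could close the gap, but it has no operating rule. In an open-label, single-arm trial, the denominator could then be settled after outcomes are known.

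The stake is the decision on a randomized trial. An active regimen could be passed over, and the quoted power may not belong to the analysis that is reported.

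**Working it through.** **Inputs.** From 16.1: p0 = 0.43, p1 = 0.63, one-sided alpha 0.10, n = 27. The Protocol gives no unassessed fraction, so q is an assumption, shown from 5% to 15%.

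**1. The plan's own figures.**
- Null: 188/435 = 0.432.
- Sample size by normal approximation: n = [(1.2816·√(0.43·0.57) + 0.8416·√(0.63·0.37)) / 0.20]² = 27.08.
- Power at n = 27: Φ{[(p1 − 0.43)·√27 − 1.2816·√(0.43·0.57)] / √(p1(1 − p1))}. For p1 = 0.53, 0.58, 0.63 and 0.68 this gives 40.9%, 61.6%, 79.9% and 92.3%, against the stated 40%, 61%, 80% and 92%.

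The stated design reproduces as a normal approximation. With the exact binomial, the smallest cut-off holding alpha at or below 0.10 is 16 of 27:
- P(X ≥ 16 | 0.43) = 0.066 and P(X ≥ 16 | 0.63) = 0.730.
- A cut-off of 15 has alpha 0.131.

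The gap between 80% and 73% is a separate issue (approximate versus exact test) and is not caused by the denominator.

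**2. Effect of the mismatch if nobody is replaced.** Suppose 27 are treated, a fraction q is unassessed and counted as failures, q is the same in the pooled trials, and 43% and 63% hold among evaluable patients. The per-treated rates are then 0.43(1 − q) and 0.63(1 − q), while the null tested stays at 0.43.

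| q (assumed) | Per-treated null / target | Normal-approx. power | Exact power, ≥16/27 | Exact alpha, ≥16/27 |
|---|---|---|---|---|
| 0 | 0.430 / 0.630 | 80% | 73% | 0.066 |
| 5% | 0.409 / 0.599 | 69% | 61% | 0.041 |
| 10% | 0.387 / 0.567 | 56% | 47% | 0.024 |
| 15% | 0.366 / 0.536 | 43% | 35% | 0.014 |

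In whole patients, with exactly 1, 2 or 3 of 27 unassessed, P(X ≥ 16) among the remaining 26, 25 or 24 at 0.63 is 65%, 55% and 44%.

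**3. Null on the same per-treated basis, 27 treated.**

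| q (assumed) | Cut-off | Alpha | Exact power |
|---|---|---|---|
| 5% | 15 | 0.088 | 74% |
| 10% | 15 | 0.056 | 63% |
| 15% | 14 | 0.075 | 65% |

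At q = 10%, power drops by 26 points (73% to 47%). Matching the null recovers about 15 of them (47% to 63% before rounding: 62.6 − 47.4 = 15.2). The rest is the cost of losing patients from a fixed cohort of 27.

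**4. Full replacement.** Treating until 27 are evaluable needs 27/(1 − q) patients, which is 29 at q = 5% and 30 at q = 10%. If replaced patients also leave the denominator, the 16.1 design is restored and the mismatch is gone. Both conditions go beyond the text: 29 or 30 exceeds the cap in sections 6 and 9.2, and 16.4 never removes a dosed patient from the ORR denominator.

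**The case against.** The strongest reply is that the plan already handles this. Section 16.1 calls 27 evaluable patients a minimum and 16.4 allows replacement, so together they can mean enrolling until 27 are evaluable. Moreover, 16.4 asks only for confidence intervals. The test against 43% sits in 16.1 beside the evaluable count, and could be read as a test among evaluable patients.

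Two further points limit the figures. The 63% is not labelled per evaluable patient; if it means treated patients, power at the target does not fall with q and only the conservative alpha remains. And q may be small: entry requires ECOG 0–1, measurable disease and life expectancy above 6 months, and imaging is every 6 weeks.

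These points stand as limits on size. A reader might infer that an active combination will be judged against too high a bar. The documents do not support that as a certainty, because replacement with removal from the denominator would undo it.

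They do not show that the plan is settled. Replacement has no trigger or limit and cannot be reconciled with 27 treated. Dropping replaced patients would also sit badly with Appendix E, which counts non-assessable patients as failing to respond and bases conclusions on all eligible patients.

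**Conclusion.** The concern holds as an unresolved inconsistency. The null and sample size in 16.1 are per evaluable patient, the ORR in 16.3 and 16.4 is per patient dosed, and the clause that might connect them is undefined and conflicts with the enrolment cap.

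The consequence is conditional. Without replacement, the comparison with 43% is conservative and the 80% power does not apply to the 16.4 analysis. The direction is towards missing an active regimen; the mismatch does not inflate the type I error.

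The size cannot be fixed from the document. The figures above rest on an assumed q that is equal in both data sets, on no replacement, and on reading 63% per evaluable patient. What evaluable meant in the pooled trials cannot be checked here.

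**What to change.** Use one denominator for null, target, sample size and ORR, fixed before data are seen.

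**Preferred.**
- Keep the per-treated ORR of 16.4 and delete the exception for replaced patients.
- Re-extract responders over treated patients from the same pooled trials as p0, and state the target on that basis.
- Change 27 evaluable to 27 treated in 16.1, and restate the cut-off and the exact power.
- Report the per-evaluable rate against 43.2% as a secondary description.

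**If the publications do not give the numbers treated.**
- Define evaluable and a binding replacement rule in advance.
- Make the 27-treated cap in sections 6 and 9.2 consistent with that rule.
- Test the per-evaluable rate against 43%, and report the per-treated rate alongside.

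**Cost.** The preferred route needs a second pass through the publications and revised text, but no extra patients. Its price is a lower stated power: about 63% to 74% exact for q between 5% and 15%, below the planned 80%. The alternative means treating more than 27 patients whenever any are unassessed.

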### 2. RATIONALE FOR THE USE OF VINORELBINE

Vinorelbine is a semi-synthetic vinca-alkaloid, derived from *vinca rosea*. Vinca alkaloids

are structurally similar compounds comprised of two multiringed units, vindoline and catharanthine. Vinorelbine differs from the natural compound by the presence of an eight-member catharanthine ring, site of structural modification.

Vinorelbine has activity in a broad spectrum of tumors, as a mitotic spindle poison that impairs chromosomal segregation during mitosis and blocks cells at G2/M, at concentrations close to the  $IC_{50}$ , between 1 and 50 nM. Microtubules are the principal target of vinorelbine, as the eight-member catharanthine ring forms covalent reversible bonds with tubulin, the monomeric subunit of microtubules. Interestingly, vinorelbine shows a preferential binding to mitotic rather than axonal microtubules, possibly determining its tumor selectivity and low neurotoxicity.

Disorganization of the microtubule structure, through induction of p53 and activation/inactivation of several protein kinases, eventually triggers apoptosis.

In metastatic breast cancer single-agent vinorelbine shows activity equivalent to many standard agents, including anthracyclines, with a response rate for first line treatment of 35-60%, documented by several phase II trials worldwide.

In the largest phase II trial on single-agent vinorelbine as first line treatment for metastatic breast cancer, 145 women received 30 mg/m^2 weekly. The overall response rate was 41%, and 30% of patients had stable disease. The median time to treatment failure was 6 months, and median survival is 18 months.

Previous therapy with anthracyclines or CMF regimen does not appear to have any influence on response.

Similar response rates (50%) are observed with vinorelbine at 25 mg/m^2 weekly, or in elderly patients, for whom no need of dose-reduction is reported.

Vinorelbine can also be administered on days 1 and 8 of 21-day cycles, to better fit the two main treatment periodicities (corresponding to one week and three weeks), with no decrease in the administered dose intensity.

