#### **5.1 Primary Objectives**

**Phase I:** To assess the optimal dose of sorafenib in combination with vinorelbine.  
**Phase II:** To assess the clinical benefit (response rate + disease control rate) in women with metastatic breast cancer, when treated with this combination at the optimal doses.

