## 16.2 Definition of study outcomes

|                         |                                                                                                                                                             |                                                                                                                 |                                                                                                         |                           |                                                                                                            |                                                                                                          |                                 |                       |
|-------------------------|-------------------------------------------------------------------------------------------------------------------------------------------------------------|-----------------------------------------------------------------------------------------------------------------|---------------------------------------------------------------------------------------------------------|---------------------------|------------------------------------------------------------------------------------------------------------|----------------------------------------------------------------------------------------------------------|---------------------------------|-----------------------|
| Objective response (OR) | Confirmed complete response (CR) or partial response (PR), defined according to RECIST criteria, persisting $\geq 4$ weeks after the initial documentation. | Confirmed objective responses plus confirmed stable disease (SD $\geq 24$ weeks), according to RECIST criteria. | Time from the first dose of study medication to the first documentation of an objective tumor response. | Duration of response (DR) | Time from the first dose of study medication to the first documentation of an objective tumor progression. | TTP will be censored at the date of death for patients who have not had objective disease progression.   | Progression-free survival (PFS) | Overall survival (OS) |

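### The Phase II primary objective is clinical benefit, but the only null, target, power and go statement are for objective response, so clinical benefit has no benchmark and is not ranked against ORR

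*Protocol*

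**What the plan says.** Three sections of the protocol set up the Phase II inference.

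- **Section 5.1** gives a single Phase II primary objective: "To assess the clinical benefit (response rate + disease control rate) in women with metastatic breast cancer". Section 16.2 defines clinical benefit as "Confirmed objective responses plus confirmed stable disease", where the stable disease (SD) must last at least 24 weeks.
- **Section 16.1** works with objective response throughout. The historical rate comes from "188 objective responses out of 435 evaluable patients". The effect of interest is "an increase from ~43% to 63% of response rate (+ 20" points), and the same sentence says that such a rise would justify a randomized trial. The test is described as "A binomial test with a nominal 0.10 one-sided significance level will have the power as shown below for various response rates". That sentence goes on to fix the null at 43%, again for response, and the number of patients at 27.
- **Section 16.4**, whose heading speaks of primary endpoints in the plural, counts confirmed responses and stable disease "to determine objective response rate (ORR) and clinical benefit rate (CBR"), each with an exact 95% confidence interval. It gives no null, target or threshold for CBR and no order between the two.

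The protocol reports no historical CBR for vinorelbine. The nearest figure is in section 2, for the largest first-line trial of the single agent: "The overall response rate was 41%, and 30% of patients had stable disease".

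**The concern.** The endpoint that section 5.1 calls primary is not the one for which section 16.1 states a hypothesis. A reader of the final report could not say, from the protocol, what CBR would count as a success or with what error rate. With two endpoints under the primary heading and no hierarchy, the choice of which to stress can be made after the data are seen.

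The 43% null offers no way out. Every confirmed responder also counts towards CBR, so CBR can never fall below ORR, and any durable stable disease on vinorelbine alone puts its CBR above its own response rate. If 43% were applied to CBR, vinorelbine with no added effect from sorafenib could pass more often than the nominal one-sided 10%. This single-arm trial exists to decide whether a randomized trial should follow, so the endpoint and benchmark behind that decision are its main inferential rule.

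**Working it through.** **Inputs.** From section 16.1: p0 = 0.43, p1 = 0.63, one-sided alpha 0.10, n = 27. From section 2: vinorelbine alone, ORR 41%, SD 30%. Not given: the share s of that SD lasting at least 24 weeks, so s is varied from 0 to 1.

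**1. The plan's own figure.** Normal approximation without continuity correction:

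power = Φ{[(p1 − p0) − z(0.90)·√(p0(1 − p0)/n)] / √(p1(1 − p1)/n)}

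At p1 = 0.63: (0.20 − 1.2816 × 0.0953)/0.0929 = 0.838, and Φ(0.838) = 79.9%. At 53%, 58% and 68% the formula gives 40.9%, 61.6% and 92.3%. The protocol states 40%, 61%, 80% and 92%. The required n is 27.1. The design therefore reproduces, for objective response. For clinical benefit there is no stated figure to reproduce.

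**2. Cut-off for the 43% null.** Exact binomial, n = 27:

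- P(X ≥ 15 | 0.43) = 13.1%, above 10%.
- P(X ≥ 16 | 0.43) = 6.6%, so the exact 0.10 rule is at least 16 of 27.

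The normal approximation puts the limit at 0.43 + 1.2816 × 0.0953 = 0.552. That is 14.9 of 27, so 15 of 27 is shown as a second column below.

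**3. CBR for vinorelbine alone.** CBR = 41% + 30% × s, which runs from 41% (s = 0) to 71% (s = 1).

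**4. Chance that vinorelbine alone passes if 43% is applied to CBR.**

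| s | CBR | P(X ≥ 16) | P(X ≥ 15) |
|---|---|---|---|
| 0 | 41% | 4.3% | 9.1% |
| 0.25 | 48.5% | 17.7% | 29.4% |
| 0.50 | 56% | 44.5% | 59.8% |
| 0.75 | 63.5% | 74.8% | 85.5% |
| 1 | 71% | 93.6% | 97.3% |

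At a CBR of 45% the exact rule passes with probability 9.8%. It crosses 10% at a CBR of 45.1%, which needs (45.1 − 41)/30, about 14%, of the stable disease to last 24 weeks.

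**5. What a CBR null would require at n = 27.** If the CBR values 48.5%, 56%, 63.5% and 71% were taken as the null, the exact one-sided 0.10 cut-off would be 17, 19, 21 and 23 of 27. Power for a 20-point gain would be 79.8%, 82.1%, 85.5% and 91.0%. Exact power moves in steps: over nulls from 46% to 66% it ranges from about 69% to about 87%. So 27 patients might still serve a CBR design, but with a different null, cut-off and power from those stated.

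**The case against.** The best defence is that the protocol does identify the deciding endpoint. Section 16.1 ties the go statement to response rate, the null and the power table are for response rate, and ORR is one of the two endpoints listed in section 16.4. Section 5.1 itself mentions response rate in its parenthesis. All of this stands. It would therefore be too strong to say that the protocol is silent on what drives the go decision, or that the trial was not sized for any primary endpoint. What remains is narrower: section 5.1 is worded around the endpoint without a hypothesis, and section 16.4 does not repeat the priority that section 16.1 implies.

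A reader might also infer that the protocol will test CBR against 43%, or declare success on either endpoint, and so has an inflated error rate. The documents do not support that. For CBR, section 16.4 plans an interval only. The probabilities above show why the benchmark does not transfer; they are not the operating characteristics of a stated rule. At the low end, where no stable disease lasts 24 weeks, the chance is 4.3%, below the nominal level. The 41% and 30% also come from one trial of weekly dosing, whereas this study gives vinorelbine on days 1 and 8 of 21-day cycles, and section 2 does not say whether those responses were confirmed.

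Finally, there is a case for keeping clinical benefit prominent, since section 3 describes sorafenib as acting mainly by stabilizing disease. That bears on which repair to choose, not on whether one is needed. A statistical analysis plan could not settle the matter without overriding either section 5.1 or section 16.1.

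**Conclusion.** The mismatch holds. The Phase II primary objective has no hypothesis, benchmark, power or error rate, and the two listed primary endpoints have no stated hierarchy. This follows from sections 5.1, 16.1 and 16.4 alone and needs no assumption.

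That 43% is unusable for CBR follows from the definition in section 16.2. The size of the error if it were used is conditional: from 4% to 94% under the exact rule of 16 of 27, passing 10% at a CBR of about 45%. This range assumes that the one cited trial represents vinorelbine alone, with the share of stable disease lasting 24 weeks unknown. The stated design reproduces for objective response under the normal approximation, so this point does not question the 27 patients as a sample size for ORR.

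**What to change.** In sections 5.1, 16.1 and 16.4, state that:

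- confirmed ORR is the Phase II primary endpoint;
- the test against 43% and the decision to proceed to a randomized trial apply to ORR only;
- CBR, as defined in section 16.2, is secondary or supportive, is estimated with its exact interval, is not compared with 43%, and cannot by itself support a go decision.

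Section 5.2 would then list clinical benefit. This changes wording only and adds no patients or procedures. Its price is that clinical benefit loses its status as the deciding primary endpoint.

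If the sponsor prefers CBR to decide, section 16.1 must give a justified vinorelbine-alone CBR null and a target, using stable disease of at least 24 weeks, and restate the cut-off and power at n = 27. That depends on whether the pooled trials report stable disease of that duration, which the protocol does not show.
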